
## MIND-BODY SKILLS TRAINING FOR ADULTS WITH NEUROFIBROMATOSIS

CI: 0.17-11.34;  $P=.056$ ], Social Relations QoL [10.95; 95% CI: 1.57-20.31;  $P=.021$ ], Environmental QoL [8.02; 95% CI: 2.57-13.48;  $P=.005$ ], and anxiety [-2.32; 95% CI: -3.96 to 0.69;  $P=.006$ ] compared to those in HEP-NF; gains maintained at follow-up. Patients in the 3RP-NF did not improve more than those in HEP-NF on depression, with both groups showing improvement. Patients in the 3RP-NF with baseline pain  $\geq 5$  of 10 showed improvement in pain intensity from baseline to post test [1.30; 95% CI: -2.26 to -.34;  $P=.009$ ] with effects maintained at follow-up; this improvement was not greater than HEP-NF. There were more treatment responders in the 3RP-NF ( $P<.05$ ). Please see appendix for full results from the paper currently in press.

Table 1. Unadjusted baseline, posttest and 6 months follow-up scores for outcomes.

| Assessment                             | Baseline      | Post test     | Follow up     |
|----------------------------------------|---------------|---------------|---------------|
| Physical Health QoL                    |               |               |               |
| 3RP-NF                                 | 68.53 (17.76) | 76.34 (19.00) | 76.34 (14.73) |
| HEP-NF                                 | 60.94 (21.16) | 61.06 (22.21) | 60.17 (22.74) |
| Psychological QoL                      |               |               |               |
| 3RP-NF                                 | 56.90 (18.34) | 67.72 (17.87) | 68.05 (16.03) |
| HEP-NF                                 | 48.12 (18.44) | 53.36 (20.16) | 51.53 (19.43) |
| Social relations QoL                   |               |               |               |
| 3RP-NF                                 | 52.60 (26.13) | 63.28 (22.78) | 59.90 (23.13) |
| HEP-NF                                 | 57.80 (20.51) | 57.53 (22.18) | 58.79 (24.16) |
| Environmental QoL                      |               |               |               |
| 3RP-NF                                 | 72.36 (20.76) | 79.68 (17.87) | 77.64 (17.80) |
| HEP-NF                                 | 66.13 (17.77) | 65.42 (18.66) | 66.64 (20.11) |
| Depression                             |               |               |               |
| 3RP-NF                                 | 16.06 (5.56)  | 13.56 (5.13)  | 12.98 (3.94)  |
| HEP-NF                                 | 18.16 (5.28)  | 16.35 (5.26)  | 17.80 (7.67)  |
| Anxiety                                |               |               |               |
| 3RP-NF                                 | 13.59 (3.32)  | 10.42 (3.15)  | 11.60 (2.58)  |
| HEP-NF                                 | 14.53 (3.12)  | 13.68 (3.16)  | 14.52 (4.28)  |
| Pain intensity (Baseline $\geq 5$ )    |               |               |               |
| 3RP-NF                                 | 6.46 (1.59)   | 5.16 (2.83)   | 4.91 (2.34)   |
| HEP-NF                                 | 6.84 (1.42)   | 6.67 (1.94)   | 7.09 (1.62)   |
| Pain Interference (Baseline $\geq 5$ ) |               |               |               |
| 3RP-NF                                 | 3.13 (2.52)   | 2.88 (2.68)   | 1.49 (1.57)   |
| HEP-NF                                 | 5.29 (2.17)   | 5.18 (2.23)   | 5.12 (2.42)   |

Note: Values are expressed as Means and SDs

Figure 2: Improvements in Physical QoL throughout the study. Average Physical Health QoL in patients in 3RP-NF and HEP-NF at baseline, post test and 6 months follow up.

[figure not shown]

Figure 3: Improvements in Psychological QoL throughout the study. Average Psychological QoL in patients in 3RP-NF and HEP-NF at baseline, post test and 6 months follow up.

[figure not shown]

**Conclusions:** The 3RP-NF delivered via videoconferencing was highly feasible and accepted by patients, and resulted in sustained improvement in QoL. This study provides Class II evidence that for patients with neurofibromatosis a mind body program is superior to an attention placebo control in improving quality of life, and provides strong pilot data for a fully powered RCT to test whether effects of the intervention maintain with a more heterogenous population, and intervention delivered by different clinicians. Further, a larger sample size is required to fully understand whether the intervention is efficacious and durable for depression and pain interference. The fully powered RCT would also allow us to explore mechanisms of improvement through the use of mediators and moderators (see aims).

## II. SPECIFIC AIMS

The present proposal is based on qualitative formative work, an open pilot of the face-to-face 3RP-NF, and a pilot single blinded RCT of the 3RP-NF versus HEP-NF, both delivered via videoconferencing with Skype showing feasibility, acceptability, preliminary efficacy and durability. The objective of the study is to test, within a single blinded fully powered RCT, the efficacy of the 3RP-NF as compared to HEP-NF (attention control) in improving co-primary (physical and psychological quality of life) and secondary (social quality of life, environmental quality of life, depression, anxiety, pain intensity and pain interference) outcomes. **Specific aims:**

- Aim 1:** to determine the efficacy of 3RP-NF in comparison to an active control HLI on the co-primary outcomes: physical health QOL and psychological health QOL among patients with NF1, NF2 and schwannomatosis. Secondary outcomes are: social relationships QoL, environment QoL, depression, anxiety, pain, pain interference, gratitude, optimism, mindfulness, coping, social support, empathy and stress. Assessments will be conducted at baseline, post-intervention (8 weeks, primary time point), 6 and 12 months follow-ups (secondary time points). Both intervention and control are delivered via live video with Zoom.

**Hypotheses:** 3RP-NF will be more efficacious in reducing primary and secondary outcomes at post-intervention, and effects will be maintained at 6 and 12 months follow-ups, compared to HEP-NF.

- Aim 2:** to examine the degree to which treatment-dependent improvements in the primary outcomes are mediated by improvements in depression, anxiety, pain intensity, pain interference, gratitude, optimism, mindfulness, coping, social support, empathy and stress (conceptual mediators) and modified by NF type, age, race/ethnicity, learning disability and education level.

**Hypotheses:** Treatment-dependent improvements in the secondary outcomes depicted in the figure below will mediate benefits from 3RP-NR for the primary outcomes. The moderators NF type, age, and race/ethnicity will be associated with differential benefit from 3RP-NF for the primary outcomes.

## III. SUBJECT SELECTION

Participants will be N = 224 adult patients (18 or older) with a diagnosis of NF1, NF2 or schwannomatosis. We will use a stratified randomization to ensure that equal numbers of patients with NF1, NF2 and Schwannomatosis will be assigned to the 3RP-NF and HEP-NF. Patients will be recruited from two sources: 1) the

## MIND-BODY SKILLS TRAINING FOR ADULTS WITH NEUROFIBROMATOSIS

Neurofibromatosis clinic at MGH (900 visits/year in 2014) and 2) the Children's Tumor Foundation (CTF). Our IRB approved flyers will be posted in various areas of the hospital and emailed periodically to patients in the NF registry via CTF, which includes local (within the United States) and international (outside of the United States) patients. We have used this method of recruitment successfully in our preliminary clinical trial ([name] PI, funding from CTF). CTF has committed their support to recruitment, should this study be funded, and DoD has allowed for recruitment of patients within and outside of the United States. This method of recruitment is advantageous because it has allowed us to recruit patients from across the U.S. and Canada, thus fostering generalizability of results. We do not anticipate any difficulties recruiting, based on our success with working with this population. However, if difficulties occur, we plan to expand our recruitment to other U.S. NF centers with whom we have collaborations, including Children's Hospital in Boston and Johns Hopkins NF Clinic. We will also be recruiting by posting our study on Partners Clinical Trials.

Recruitment will also occur through the Research Patient Database Registry (RPDR). The RPDR is a centralized clinical data registry that gathers data from various hospital legacy systems and stores it in one place. Researchers access the data using the RPDR online Query Tool. They may query the RPDR data for aggregate totals, and with proper IRB approval, obtain medical record data. The RPDR ensures the security of patient information by controlling and auditing the distribution of patient data within the guidelines of the IRB and with the use of several built-in, automated security measures. To identify potentially eligible patients:

- 1) A RPDR query will be performed to identify those patients with chronic pain diagnoses. Study staff will review the medical record to confirm potential participant eligibility and to identify their linkage to an MGH primary care physician. Access to patients' medical records will be restricted to this pre-enrollment recruitment phase.
- 2) Study staff then will obtain permission for initial contact from each potentially eligible patient's PCP by having providers review letters and discard ones that they do not approve.
- 3) For physician-approved patients, study staff will send a study introduction letter from the patient's physician (with the clinician's name at the bottom) and a study opt-out letter signed by [name] (PI). The letter from the PCP informs the patient that he or she is allowing the study to contact patients with chronic pain in case they are interested in learning about the study. [name] letter is an opt-out letter describing the study, the procedure to opt out of further contact, and whom to call for further information.
- 4) Should study staff receive no reply within 10 days, staff members will call the patient on the phone to assess interest in the study and to describe the study over the phone. If the patient remains interested, staff will confirm eligibility and assess for inclusion and exclusion criteria.

For potentially eligible patients who are enrolled in the MGH Research Options Direct to You (RODY) Program, we will send them an opt-out letter and call 10 days later to inform them about the study. RODY identifies patients who are willing to be contacted directly about research studies. Patients who have agreed to be contacted directly are identifiable through the RPDR search; each patient's RODY status is available in the demographics table included in the RPDR output.

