52.91), the physical functioning (M = 64.79) and social (M = 55.15) subscales were significantly lower than those of the general population ( $p < .05$ ). Scores on resilience, a construct that increases with age, were not significantly different from college students, but were significantly lower than those of older adults ( $p < .05$ ). Scores on Gratitude (M = 32.31) and emotional support (M = 27.85) scales were also significantly lower than normal population scores ( $p < .05$ ). There was a great deal of variability in all pain assessments. The mean score on pain intensity (M = 4.43, range 0-10), and mean scores on PCS (M = 16.6, range 0-57) and BPI (M = 19.66, range 0-65) were significantly lower than those of patients with back pain ( $p < .05$ ) and cancer pain ( $p < .05$ ), respectively. There were no significant differences in any of the study measures among patients with NF1, NF2 and schwannomatosis ( $p > .05$ ), except on pain intensity, where patients with schwannomatosis reported pain scores significantly higher than patients with NF1 and NF2. In sum, patients with NF have significant psychological distress and difficulties coping compared to general population, and these difficulties are similar among patients with NF1, NF2 and schwannomatosis. This reinforces the need of psychosocial skills based interventions for this population and suggests that patients with NF1, NF2 and schwannomatosis can be grouped together as participants in such interventions.

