### Inclusion/Exclusion Criteria

Inclusion and exclusion criteria were selected following guidelines for psychosocial treatment development and for bridging efficacy with effectiveness. Women and minorities will not be excluded. Screening will be done through patient self-report either in person (when patients are recruited from the MGH NF clinic) or via Zoom (when patients are recruited through CTF).

| Inclusion Criteria                                                    | Exclusion Criteria                                                                       |
|-----------------------------------------------------------------------|------------------------------------------------------------------------------------------|
| 1. Has a diagnosis of NF1, NF2 or schwannomatosis and is 18 or older. | 1. Has major medical comorbidity not NF related expected to worsen in the next 12 months |

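### The RPDR recruitment procedure selects on chronic pain instead of on neurofibromatosis, so this supplementary route misses NF patients without a pain diagnosis and selects on pain those it finds

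*Protocol*

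**What the plan says.** Section III (Subject Selection) of the protocol defines the population by NF diagnosis alone: "Participants will be N = 224 adult patients (18 or older) with a diagnosis of NF1, NF2 or schwannomatosis". The Inclusion/Exclusion Criteria table repeats this as its first inclusion criterion: "Has a diagnosis of NF1, NF2 or schwannomatosis and is 18 or older". The other four inclusion criteria cover consent and English, reading level, self-reported difficulty coping, and a PSS-4 score of 6 or higher. None mentions pain.

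Section III first names two sources of patients, the NF clinic at the study hospital and the Children's Tumor Foundation (CTF). It then adds a registry route: "Recruitment will also occur through the Research Patient Database Registry (RPDR"). This route has four numbered steps:

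- Step 1 sets the query: "A RPDR query will be performed to identify those patients with chronic pain diagnoses". It then adds a chart check: "Study staff will review the medical record to confirm potential participant eligibility".
- Step 2 asks the primary care physician of each potentially eligible patient for permission to make contact.
- Step 3 mails two letters to approved patients. The physician's letter says that he or she is "allowing the study to contact patients with chronic pain in case they are interested in learning about the study". The second is an opt-out letter describing the study.
- Step 4 is a phone call, in which "staff will confirm eligibility and assess for inclusion and exclusion criteria".

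A further paragraph covers patients in the direct-contact (RODY) programme, who are identifiable through the RPDR search. Neither the four steps nor that paragraph names NF1, NF2 or schwannomatosis.

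**The concern.** The query is an operative instruction, and it names a different population from the one the trial studies. The same wording recurs in a patient-facing letter, so it is hard to read as a single slip of the pen. Nothing else in the protocol corrects it or gives a reason for selecting on pain.

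Four things are at stake: NF patients the registry could supply but the query would not return; chart access for patients whom the trial does not concern; a physician's letter giving a basis for contact that does not match the study; and selection on a variable the trial analyses. Pain intensity and pain interference are secondary outcomes in Section II, and Section V lists both pain instruments as secondary outcomes and mediators. The protocol also claims generalizability for its recruitment, both in Section III and under Recruitment.

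**Working it through.** No figure in the plan needs reproducing. The check sets the passages side by side and follows the route in order.

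**1. Target against query.**

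| Item | Place in protocol | Selects on |
|---|---|---|
| Population of 224 | Section III, opening | NF1, NF2 or schwannomatosis; age 18 or older |
| Inclusion criterion 1 | Inclusion/Exclusion Criteria | the same |
| Inclusion criteria 2 to 5 | Inclusion/Exclusion Criteria | no pain requirement |
| RPDR query | Section III, step 1 | chronic pain diagnosis; NF not named |
| Physician's letter | Section III, step 3 | chronic pain; NF not named |

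**2. Who is found.** The query returns registry patients with a chronic pain diagnosis. After chart review, those left for this trial are patients with both NF and a pain diagnosis. NF patients without a pain diagnosis are never returned, and no later step can recover them, because each works only on what step 1 supplies. The RODY paragraph depends on the same search.

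**3. Who is contacted and enrolled.** Chart review for eligibility stands in step 1, before physician permission (step 2) and mailing (step 3). Inclusion and exclusion criteria are assessed again by phone in step 4. The excess burden therefore falls on record review; there is no written path by which patients without NF should be mailed or enrolled.

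**4. Selection on pain.** Every NF patient who enters through this query carries a chronic pain diagnosis. In the protocol's own NF sample (Section I, Study 4), mean pain intensity was 4.43 on a 0 to 10 scale, and "There was a great deal of variability in all pain assessments". Requiring a pain diagnosis is therefore a real restriction. Study 4 also reports higher pain intensity in schwannomatosis than in NF1 and NF2, so the NF-type mix of this subset could shift too.

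**5. Size.** Let f be the fraction of enrolled patients who come through the RPDR, and p the proportion of patients from the other sources who have a chronic pain diagnosis. The proportion with a pain diagnosis in the whole sample is

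f × 1 + (1 − f) × p

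and the shift relative to the other sources is

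f + (1 − f)p − p = f(1 − p).

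The document gives neither f nor p. All that can be said is that the shift lies between 0 and f: it cannot exceed the RPDR share of enrolment, and it vanishes if the route supplies nobody.

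**6. Effect on the comparison.** Selection through the RPDR happens before randomisation. Section V allocates 1:1 in permuted blocks stratified by diagnosis, so both arms draw on the same recruited pool. The case mix may change, but the contrast between 3RP-NF and HEP-NF is not biased by it.

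**The case against.** The strongest reply is that the mismatch has little consequence. The RPDR is an addition to the NF clinic and CTF, and the Recruitment subsection reports 255 inquiries from one CTF email in the pilot, against a target of 224 here. Chart review and phone screening protect eligibility. The opt-out letter mailed with the physician's letter describes the study, and its text is not shown, so recipients may well learn that the study concerns NF. Baseline NRS pain is also planned as a covariate among the sensitivity models in Section VI.3.

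Most of this stands, and it limits the point. It also rules out several stronger readings:

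- A reader might infer that letters would go mainly to ineligible people. The written order does not support this, because chart review comes first.
- A reader might infer that the NF yield would be close to nil. The protocol gives no registry count and no overlap between NF and pain diagnoses. A near-zero yield would also leave almost no room for a shift in case mix, so the two claims cannot both be pressed.
- A reader might infer a shift in physical quality of life, a co-primary outcome. This is conceivable in the RPDR subset, but the protocol offers nothing to size it.

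The reply does not remove the contradiction. Screening can discard patients without NF, but it cannot supply NF patients whom the query never returned. Covariate adjustment does not change who was sampled. A clear opt-out letter would not correct the physician's letter beside it.

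**Conclusion.** The point holds as an inconsistency in a supplementary recruitment procedure that should be corrected. As written, RPDR steps 1 and 3 select and address patients by chronic pain, while the trial enrols by NF diagnosis with no pain criterion. The missed NF patients, the unneeded chart review, the misstated basis for contact in the physician's letter and the selection on pain within this subset all follow from the text.

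The size is undetermined. The shift in the proportion with a pain diagnosis is f(1 − p), bounded by the RPDR share of enrolment, and the protocol gives neither quantity. The conclusion assumes that staff run the query as written and that chart review and phone screening work as described. On those assumptions the effect is confined to recruitment and to the generalizability of the RPDR-sourced subset. A reader might go further and infer that ineligible patients would be enrolled or that the treatment comparison would be biased; the screening steps and the randomisation give no support for either.

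**What to change.** In Section III, RPDR step 1, define the query by diagnoses of NF1, NF2 and schwannomatosis in place of chronic pain. In step 3, reword the physician's letter so that it refers to patients with neurofibromatosis (NF1, NF2 or schwannomatosis). The other steps can stay as they are, and the RODY paragraph is corrected along with the search it relies on.

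The cost is an IRB amendment to protocol and letter wording. No extra patients, visits, staff or analyses are needed.

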### Inclusion/Exclusion Criteria

Inclusion and exclusion criteria were selected following guidelines for psychosocial treatment development and for bridging efficacy with effectiveness. Women and minorities will not be excluded. Screening will be done through patient self-report either in person (when patients are recruited from the MGH NF clinic) or via Zoom (when patients are recruited through CTF).

| Inclusion Criteria                                                    | Exclusion Criteria                                                                       |
|-----------------------------------------------------------------------|------------------------------------------------------------------------------------------|
| 1. Has a diagnosis of NF1, NF2 or schwannomatosis and is 18 or older. | 1. Has major medical comorbidity not NF related expected to worsen in the next 12 months |

## MIND-BODY SKILLS TRAINING FOR ADULTS WITH NEUROFIBROMATOSIS

|                                                                                                                                       |                                                                                                                                                                                                                    |
|---------------------------------------------------------------------------------------------------------------------------------------|--------------------------------------------------------------------------------------------------------------------------------------------------------------------------------------------------------------------|
| 2. Is capable of completing and fully understanding the informed consent process and the study procedures and assessments in English. | 2. Recent (within past 3 months) change in antidepressant medication                                                                                                                                               |
| 3. At least a 6 th grade self-reported reading level.                                                                      | 3. Recent participation in cognitive behavioral therapy or relaxation therapy (within past 3 months)                                                                                                               |
| 4. Self reported difficulties coping with stress and NF symptoms.                                                                     | 4. Has significant mental health diagnosis requiring immediate treatment (e.g., untreated bipolar disorder, psychotic disorder, active substance dependence)- by self report and observation during pre-screening. |
| 5. Score of 6 or higher on the PSS-4.                                                                                                 | 5. Unable or unwilling to complete assessments electronically via REDCap.                                                                                                                                          |
|                                                                                                                                       | 6. Unable or unwilling to participate in group videoconferencing sessions.                                                                                                                                         |

